### Recruitment and randomization

Potential participants will be recruited from hospital outpatient clinics across multiple centers. Individuals interested in participating will be provided with detailed information about the study protocol, followed by a discussion of study procedures and a screening visit about health and medical history based on inclusion and exclusion criteria via telephone or web. Potential participants will be informed that they will be randomly assigned to either the CR diet group or the metformin group, and that they will not be able to choose their group. Individuals who meet any of the exclusion criteria will be deemed ineligible. Eligible participants will be required to provide written informed consent and complete all baseline assessments before randomization. Block randomization will be performed using a computer-generated random number sequence (command RALLO in SAS) with a fixed block size of 10 to ensure balanced allocation between the two groups across centers. Group assignments will be prepared in sealed, opaque envelopes by a team member not involved in participant recruitment or assessment to ensure allocation concealment. The envelopes will not be revealed to participants until the completion of baseline data collection. Serum and fecal sample will be collected and stored for future use in ancillary studies. Given the nature of the interventions (a CR diet versus metformin), blinding of participants and personnel delivering the interventions is not feasible. However, outcome assessors and data analysts will be blinded to treatment allocation. Outcome assessors will not have access to participants’ treatment allocation information during outcome ascertainment. For statistical analyses, treatment groups will be coded using non-identifying group labels, and data analysts will remain blinded to the corresponding intervention assignments until the prespecified primary analyses have been completed. These procedures are intended to minimize potential assessment and analytical bias. The research protocol, V1.0, was completed on 1 April 2023.

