## Methods

### Study design

This multicenter, randomized (1:1) comparative effectiveness trial will be conducted to evaluate and compare metabolic and reproductive outcomes between a CR diet and metformin over a 12-week period prior to OI therapy in women with PCOS and overweight/obesity from numerous hospitals nationwide in China. Female participants meeting the predefined eligibility criteria will be recruited, after which eligible subjects will be randomly assigned to either the CR diet group or the metformin intervention group. Following the intervention, standard OI therapy will be administered to participants in both study groups, and subsequent pregnancy outcomes will be monitored. The study flow chart is illustrated in Figure 1. The trial protocol has been designed and is reported according to the Standard Protocol Items: Recommendations for Interventional Trials (SPIRIT) (see Supplementary Material), and the trial results will be reported in accordance with the Consolidated Standards of Reporting Trials (CONSORT). The study protocol has received ethical approval from the Ethics Committee of Shanghai First Maternity and Infant Hospital (Approval Number: KS23168). All procedures involving human participants are in accordance with the ethical standards of the institutional research committee. Written informed consent will be obtained from all participants prior to enrollment. This study was registered at ClinicalTrials.gov (NCT06049186) on 14 September 2023.

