### Sample size

According to the literature (41, 42), live birth rates among women with PCOS in the control arm were around 31.0%. Based on findings from other studies in fertility care and expert opinions from gynecologists and epidemiologists, we assume that a minimal clinically important difference to make CR preferable over conventional diet would be 15.0% (43). To detect this difference using a two-sided test with a 5.0% alpha error and 80% statistical power, and accounting for a potential dropout rate of 20% (44), the minimum numbers of participants required for the study will be 406. Participants will be randomized in a 1:1 ratio between the intervention and control groups. No interim analysis or sample size re-estimation is planned, and the prespecified sample size will be maintained throughout the trial. As the true intervention effect may differ from that assumed in the sample size calculation, the final treatment effect will be reported with its corresponding 95% confidence interval to indicate the magnitude and precision of the observed effect.

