The primary outcome, live birth rate, will be compared between the two groups using Pearson’s chi-square test or Fisher’s exact test for unadjusted analyses. The unadjusted risk ratio (RR) and 95% confidence interval (CI) will be estimated. In addition, an adjusted analysis will be performed using multivariable Poisson regression or a log-binomial model, as appropriate, to estimate the adjusted RR and 95% CI. Prespecified clinically relevant baseline prognostic factors that are routinely available across the study population, including age, baseline body mass index (BMI), and relevant baseline PCOS-related reproductive and metabolic characteristics, will be considered in the adjusted model. Hazard ratios (HR) and 95% CI will be calculated using multivariable Cox proportional hazards analysis to compare time to live birth between groups, with adjustment for relevant prespecified baseline prognostic factors. Pregnancy rates will also be assessed using an intention-to-treat approach with Kaplan–Meier estimation, where time to pregnancy is defined as the number of days from randomization (intervention start) to the first positive pregnancy test. Between-group differences will be evaluated using the log-rank test, and multivariable Cox proportional hazards models will be applied to adjust for the prespecified baseline prognostic factors. As anti-Müllerian hormone (AMH) measurements are not available for all participants, AMH will not be included as a covariate in the primary adjusted analysis. Among participants with available AMH measurements, supplementary exploratory analyses will be conducted to assess the association between baseline AMH and reproductive outcomes and to explore whether baseline AMH modifies the relative effects of the CR diet and metformin.

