Several limitations of this study should be acknowledged. First, because of the distinct nature of the interventions, participants and personnel delivering the interventions cannot be blinded to treatment allocation, which may introduce performance bias. Nevertheless, outcome assessors and data analysts will remain blinded, and live birth, the primary outcome, is an objective clinical endpoint, which may reduce the potential for assessment bias. Second, the intensity of intervention differs between the two groups. Participants in the CR diet group receive app-based dietary monitoring, individualized dietary guidance, and regular feedback from dietitians, whereas participants in the metformin group receive pharmacological treatment with routine clinical advice. Consequently, observed between-group differences may partly reflect the additional healthcare attention, self-monitoring, and behavioral support provided as components of the CR intervention rather than calorie restriction alone. Attention bias therefore cannot be completely excluded, and the findings should be interpreted as reflecting the comparative effectiveness of the overall CR diet and metformin intervention strategies rather than the isolated physiological effects of calorie restriction versus metformin. Third, although standardized study procedures are used to promote consistency across participating centers, some center-level variability in intervention delivery and measurements cannot be completely excluded. In particular, differences in body composition assessment devices across centers may introduce measurement variability in anthropometric outcomes. Finally, the study population is restricted to women aged 20–35 years with PCOS and overweight/obesity who are eligible for OI, which may limit the generalizability of the findings to women outside this age range, women with PCOS without overweight/obesity, or those receiving other forms of fertility treatment. In addition, because the trial is conducted in China and applies an Asian-specific BMI threshold, extrapolation of the findings to populations with different ethnic, dietary, and healthcare backgrounds should be made cautiously.

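### The disclosed fixed block of 10 balances centres only if blocks are built within centre; then some allocations can be deduced, and the primary test ignores the stratum

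*Protocol article*

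**What the plan says.** Under Recruitment and randomization, the article generates the sequence by computer "with a fixed block size of 10 to ensure balanced allocation between the two groups across centers". On concealment it says: "Group assignments will be prepared in sealed, opaque envelopes by a team member not involved in participant recruitment or assessment". It adds: "The envelopes will not be revealed to participants until the completion of baseline data collection". The same section says that "blinding of participants and personnel delivering the interventions is not feasible"; outcome assessors and data analysts are blinded. Allocation is 1:1 (Sample size), and women come "from numerous hospitals nationwide in China" (Study design), with no number of centres given.

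Under Statistical analysis, the primary comparison of live birth is an unadjusted Pearson chi-square or Fisher exact test. A Poisson or log-binomial model follows, for which prognostic factors, "including age, baseline body mass index (BMI), and relevant baseline PCOS-related reproductive and metabolic characteristics, will be considered in the adjusted model". The Cox, log-rank and mixed-effects analyses do not name centre either. The limitations in the Discussion concede that "some center-level variability in intervention delivery and measurements cannot be completely excluded".

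**The concern.** Two matters hang on one sentence.

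**Concealment.** The stated safeguards cover who prepares the envelopes, when the participant learns her group, and blinding at outcome assessment and analysis. None of them addresses a staff member who counts earlier assignments. With a fixed, known block size, the end of each block follows from that count however opaque the envelope is. Someone with foreknowledge could delay or bring forward a woman's enrolment, and blinded ascertainment of live birth cannot undo selection at entry.

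**Analysis.** The stated purpose, balance across centres, is met only by blocking within centre. A single list in blocks of 10 balances the total, not each hospital. If blocking is within centre, centre is a randomisation stratum, and the primary test leaves it out. At stake there is efficiency and the width of the interval.

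**Working it through.** **Inputs.** From the article: block of 10, ratio 1:1, control live birth rate 31%, difference 15 points, two-sided alpha 5%, power 80%, dropout 20%, total 406. Assumed, because the article gives no centre count or spread: 10 centres of 40 women (20 per arm), with a between-centre SD of 0 to 1.0 in log-odds.

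**The plan's own figure.** With unpooled variance, n per arm = (1.960 + 0.842)² × (0.31×0.69 + 0.46×0.54) / 0.15² = 7.849 × 0.4623 / 0.0225 = 161.3, so 162. Allowing for dropout, 162/0.8 = 202.5, so 203 per arm and 406 in total. This matches, and nothing below changes it.

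**Allocations known with certainty.** In a block with m = 5 per arm, an allocation is certain once one arm is used up. The expected number is 2m/(m+1) = 10/6 = 1.67 per block, or 16.7%. Enumerating all 252 sequences agrees. At least one allocation is certain in every complete block, two or more in 44.4% and three or more in 16.7%. At most 40 complete blocks fit into 406, so the ceiling is about 40 × 1.67 = 67 women. It is lower in practice, because each centre is likely to stop part-way through a block.

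**Best guess.** Always guess the arm with more places left. The expected number correct per block is m − ½ + 2^(2m−1)/C(2m,m) = 4.5 + 512/252 = 6.53, or 65.3%, against 50% by chance.

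**The same guess under varying blocks** (simulated sequences of 406, guessing the arm that is behind):

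| Block sizes | Correct guesses |
|---|---|
| fixed 10 | 65.2% |
| 6, 8, 10 | 66.4% |
| 4, 6, 8 | 68.1% |
| 4, 6 | 69.3% |

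If the sizes are varied and undisclosed, the end of a block is unknown and nothing can be deduced with certainty. The average guess does not become harder.

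**Leaving out centre after balancing on it.** Let p_c be the live birth rate in centre c and p the overall rate. The unstratified test uses p(1−p), which equals the mean of p_c(1−p_c) plus the between-centre variance of p_c. Balance within centre has already removed that second term from the arm difference, so the test's standard error is too large. A hand check at log-odds SD 0.5: the SD of p_c is about 0.5 × 0.31 × 0.69 = 0.107 and its variance 0.0114. The share is 0.0114/0.2139 = 0.053, the effective critical value 1.96/√0.947 = 2.014, and the type I error about 0.044.

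Simulation (20,000 null trials and 5,000 with a 15-point effect per setting):

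| Centre SD | Type I, unstratified | Type I, stratified | Power, unstratified | Power, stratified |
|---|---|---|---|---|
| 0 | 0.050 | 0.050 | 0.873 | 0.875 |
| 0.3 | 0.051 | 0.052 | 0.871 | 0.877 |
| 0.5 | 0.043 | 0.047 | 0.877 | 0.888 |
| 0.8 | 0.038 | 0.049 | 0.883 | 0.905 |
| 1.0 | 0.036 | 0.054 | 0.880 | 0.910 |

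A separate set of 20,000 null trials gave 0.046, 0.044 and 0.037 unstratified at SD 0.3, 0.5 and 0.8. The effect is therefore hard to tell from simulation noise at SD 0.3 and clear from about 0.5. Power exceeds 80% because 200 per arm are analysed rather than 162.

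**The case against.** The strongest reply is that the article does not say that blocks are within centre, that recruiters know the block size, or that they can see past allocations. It says only that delivery staff are unblinded. With one central list, a site could not readily follow the blocks. This stands, and it makes the deduction figure conditional. It does not rescue the sentence, because a central list would not secure the balance that is claimed.

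Existing safeguards also count. Eligibility, written consent and all baseline assessments come before randomisation, and someone outside recruitment prepares the envelopes. They narrow the scope for steering largely to the timing of enrolment. A block of 10 is already large, and on average harder to guess than smaller varied ones.

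On the analysis, the covariate list is introduced by a word that leaves it open, and the random effects of the mixed models are not given. A separate analysis plan could add centre there. The unstratified primary test, however, is stated outright.

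A reader might infer from the Discussion that live birth itself is expected to differ between centres. The text does not go that far: the sentence concerns delivery and measurement, with body-composition devices as its example. The centre spread used above is therefore an assumption.

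**Conclusion.** The point holds in conditional form. The stated purpose of the blocks requires blocking within centre. If that is what is done, a fixed and disclosed size leaves on average 1.67 of 10 allocations deducible by staff who know the size and keep a tally, and the primary test omits the randomisation stratum.

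Two stronger readings are not supported. One is that sites can in fact predict allocations: this needs facts about the lists and about staff access that the article does not give. The other is that omitting centre makes the result invalid or raises false positives. The direction is the opposite: type I error of about 0.036 to 0.050 and up to about 3 points of power lost, under the assumed 10 centres of 40 and SD of 0 to 1.0. With little centre spread the loss is negligible.

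The change is still worth making. Selection at entry cannot be repaired afterwards, and analysing by the stratum costs almost nothing. The sample size is unaffected.

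**What to change.** 1. State that blocks are built within centre. If a single list was used, withdraw the claim that it balances the groups across centres.
2. For any participants still to be randomised, use permuted blocks of randomly varying, undisclosed sizes stratified by centre. Ideally, release each allocation centrally once baseline data are complete, if the electronic data capture system supports this; the article describes that system only for data entry and checks. The gain is that no allocation is known with certainty; it is not a lower guess rate.
3. If blocks are within centre, test live birth with a centre-stratified Cochran-Mantel-Haenszel test, and add centre (small centres pooled by a rule fixed in advance) to the adjusted risk-ratio, Cox and mixed models.
4. Add the concealment limitation to the Discussion.

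The cost is small set-up work, slightly larger chance imbalance in small centres, and one extra term per model. The article does not show whether recruitment is still open. If it has closed, item 2 falls away, and the analysis change and the disclosure remain.

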### Intervention

#### Overview

After completing baseline questionnaires, scales, and anthropometric measurements with the assistance of field investigators and dietitians, eligible subjects will be randomly assigned to either the CR diet group or the metformin group in a 1:1 ratio. Participants randomized to the CR diet group will receive standard dietary management, which includes a target energy intake assessment, a pre-intervention education session, and an app-based CR diet program consisting of an 8-week CR phase followed by a 4-week weight maintenance phase. Participants randomized to the metformin group will receive enteric-coated metformin tablets at a total daily dose of 1,500 mg. All participants will be instructed not to alter their physical activity habits throughout the trial to minimize potential confounding factors (45, 46). After the 12-week intervention period, both interventions (CR diet and metformin) will be discontinued, and all participants will undergo OI therapy (up to 5 cycles).

#### CR diet group

To implement the CR diet, the total energy expenditure (TEE) of each participant will be calculated, and the target daily energy intake will be set at 30–50% below the baseline TEE, depending on the participant’s BMI (47). Before the intervention, the International Physical Activity Questionnaire Short Form (IPAQ-SF), along with weight, height, and age, is used to estimate TEE. The model for calculating TEE is based on basal metabolic rate (BMR) and physical activity level (PAL), as recommended by FAO/WHO/UNU Expert Consultation Report (48, 49):
TEE=BMR∗PAL
(1)

In Equation 1, BMR is calculated using the Mifflin-St Jeor equation (50), which incorporates weight, height, and age, as shown in Equation 2:
$$\begin{array}{c} \mathrm{BMR}=[9.99\times \text{Weight}\;(\mathrm{kg})]+[6.25\times \text{Height}\;(\mathrm{cm})]\\ -[4.92\times \mathrm{Age}\;(\text{years})-161] \end{array}$$
(2)

The PAL value in Equation 1 is determined using IPAQ-SF, which categorizes individuals into activity levels, such as low-level physical activity, moderate-level physical activity, and high-level physical activity (51, 52). The activity levels are then assigned a corresponding PAL, for example, PAL = 1.4 for low-level physical activity, PAL = 1.6 for moderate-level physical activity, and PAL = 1.8 for high-level physical activity (49, 53).

Before the intervention, participants will receive individualized diet plans based on their calculated target energy intake and will be educated on the principles of reducing daily caloric intake. The prescribed macronutrient distribution for each participant will allocate 40–55% of total energy intake to carbohydrates, 15–20% to protein, and 20–30% to fat, aligning with the ranges recommended by current dietary guidelines (54). Participants may select foods according to their usual dietary habits and preferences while adhering to the prescribed energy and macronutrient targets. During dietary counseling, dietitians will consider regional dietary practices, food availability, and affordability to improve the feasibility and adherence to the CR diet. Participants will upload dietary records, and feedback will be provided on whether their macronutrient intake falls within the target ranges to help them maintain the prescribed distribution. In addition, participants will be instructed not to alter their physical activity habits throughout the trial to minimize potential confounding.

To enhance adherence to the diet intervention in the CR diet group, a custom healthcare service application (app) will be utilized. The app includes two components: a mobile app for participants and an administrator interface for researchers. Through the mobile platform, participants can record food diaries, communicate with dietitians, and receive messages. The dietitians and investigators can access all submitted information and interact with participants via the administrator interface.

Participants will be instructed to record their daily food and beverage consumption using household measures via the app during the 12 weeks of the intervention. Daily uploads including household measurements, photographs, and detailed food descriptions will primarily be used to support dietary adherence through self-monitoring and to provide individualized feedback on the macronutrient distribution. For an objective assessment of actual dietary intake, three 24-h dietary recalls (covering two weekdays and one weekend day) will be extracted by dietitians from participants’ uploaded food diary records. Daily dietary intake will be calculated based on the reported food types and portion sizes, using the nutrient composition data from the Chinese Food Composition Table (55). Adherence to the CR diet will be quantitatively assessed using app-based dietary records through two complementary measures: recording adherence and CR-target adherence. Recording adherence will be calculated as the number of weeks in which a participant records dietary intake on at least 3 days divided by the 12-week intervention period, multiplied by 100%. CR-target adherence will be calculated as the number of weeks in which the participant achieves the prescribed calorie-restriction target divided by the number of weeks meeting the dietary recording criterion, multiplied by 100%. For both measures, adherence will be categorized as high (≥80%), moderate (60–79%), or low (<60%).

During the first 8 weeks of the intervention, dietitians will provide individualized feedback to each participant twice a week via the app. Feedback will be informed by quantified dietary intake, comprising total energy and the macronutrient distribution (carbohydrates, protein, and fat), derived from participants’ uploaded food-diary records (55). Tailored recommendations regarding adjustments to energy intake and food choices will be subsequently issued by dietitians to ensure adherence to the CR protocol. During the subsequent 4-week weight-maintenance period, dietitians will discontinue active dietary intervention and no longer provided feedback on the CR protocol. However, participants will be required to continue recording their food diaries through the app.

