### Eligibility criteria

Inclusion criteria: (1) Women aged between 20 and 35 years, (2) body mass index (BMI) ≥ 23 kg/m^2^ based on the WHO Asian population criteria (40), (3) diagnosed with PCOS based on the Rotterdam diagnostic criteria, as updated in the 2023 International Evidence-Based Guideline for the Assessment and Management of PCOS (14). PCOS was diagnosed when at least two of the following three features were present: (a) oligo- or anovulation, (b) clinical and/or biochemical hyperandrogenism, and (c) polycystic ovarian morphology (PCOM) on ultrasound.

Exclusion criteria: (1) pre-existing type 2 diabetes mellitus, (2) uncontrolled thyroid disorders, (3) acute or chronic infections, (4) severe cerebrovascular or cardiovascular diseases or organic heart disease, (5) history of malignant tumors, (6) use of glucocorticoids or anti-androgen drugs (e.g., spironolactone, cyproterone acetate, flutamide, oral contraceptive pills) within the past 3 months, (7) congenital or acquired uterine anomalies, (8) prior bariatric surgery, (9) currently undergoing weight loss treatment and having experienced weight loss > 5% within the past 3 months, (10) severe hepatic or renal dysfunction, (11) tubal obstruction, (12) total number of motile sperm in male partner < 10 million.

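### Equation 2 as printed adds 161 where it appears meant to subtract it; if that form were used, every BMR would be 322 kcal/day too high

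*Protocol article*

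**What the plan says.** Under Intervention, CR diet group, the article gives a chain of three steps for the experimental arm.

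- **BMR.** "BMR is calculated using the Mifflin-St Jeor equation (50), which incorporates weight, height, and age, as shown in Equation 2". In plain notation, Equation 2 reads BMR = [9.99 × Weight] + [6.25 × Height] − [4.92 × Age − 161], with weight in kg, height in cm and age in years.
- **TEE.** Equation 1 multiplies BMR by a physical activity level (PAL). The values 1.4, 1.6 and 1.8 are offered as examples for low, moderate and high activity.
- **Target.** "the target daily energy intake will be set at 30–50% below the baseline TEE", with the percentage depending on BMI.

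The target is then put to use. Before the intervention, "participants will receive individualized diet plans based on their calculated target energy intake". In the first eight weeks, "Tailored recommendations regarding adjustments to energy intake and food choices will be subsequently issued by dietitians to ensure adherence to the CR protocol". The numerator of CR-target adherence is "the number of weeks in which the participant achieves the prescribed calorie-restriction target".

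**The concern.** A minus sign in front of a bracket applies to everything inside it. In Equation 2 the last bracket holds the age product and −161, so the constant enters BMR as +161.

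Two features of the printed equation suggest that this is a misplaced bracket. The weight and height brackets each hold a single product, and only the third also takes in the constant. The constant is also written with a minus sign, which is an odd way to write something meant to be added.

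Equation 2 is the only rule the article prints for setting the energy target of the experimental arm. If sites or the app followed it as written, targets would be too generous and the CR arm would receive a weaker restriction than the protocol describes. Participants could also score high adherence against those targets.

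**Working it through.** The article gives no worked BMR, TEE or target value, so there is no stated figure to reproduce. The check is algebra on the printed equation, carried through the article's own steps.

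**Inputs from the article (CR diet group):** coefficients 9.99, 6.25 and 4.92; constant 161; TEE = BMR × PAL; example PAL 1.4 to 1.8; target 30% to 50% below TEE.

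**Assumed for illustration:** a woman of 70 kg, 160 cm and 28 years (BMI 27.3), who meets the age and BMI limits under Eligibility criteria.

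**Step 1, the two forms.** Write W, H and A for weight, height and age.
- Printed: 9.99W + 6.25H − (4.92A − 161) = 9.99W + 6.25H − 4.92A + 161
- Bracket closed after age: 9.99W + 6.25H − 4.92A − 161
- Difference: 2 × 161 = 322 kcal/day, whatever the weight, height or age

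**Step 2, TEE.** The gap is 322 × PAL: 322 × 1.4 = 451, 322 × 1.6 = 515 and 322 × 1.8 = 580 kcal/day.

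**Step 3, target.** The gap is 322 × PAL × (1 − deficit).
- Smallest: 322 × 1.4 × 0.5 = 225 kcal/day
- Largest: 322 × 1.8 × 0.7 = 406 kcal/day

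Unlike the BMR gap, the target gap varies between participants. It depends on PAL and, through the BMI-based deficit, on weight and height.

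**Step 4, the assumed woman.**
- Printed BMR: 699.3 + 1,000 − (137.76 − 161) = 1,722.5 kcal/day
- Corrected BMR: 699.3 + 1,000 − 137.76 − 161 = 1,400.5 kcal/day
- Ratio: 1,722.5 / 1,400.5 = 1.2299

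| At PAL 1.4 | Target, printed form | Target, corrected form | Actual deficit if printed form used |
|---|---|---|---|
| Nominal 30% | 1,688 | 1,373 | 1 − 0.7 × 1.2299 = 13.9% |
| Nominal 50% | 1,206 | 980 | 1 − 0.5 × 1.2299 = 38.5% |

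The actual deficit is measured against the corrected TEE. PAL cancels, so it is the same at every activity level.

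**Step 5, other body sizes.** Across five assumed women (59–100 kg, 160–165 cm, 20–35 years), 322 kcal/day is about 19–25% of the corrected BMR. A nominal 30% restriction becomes about 13–17%, and a nominal 50% about 38–41%.

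**The case against.** The strongest reply is that the operative instruction is the named and cited equation, and Equation 2 merely displays it. A misplaced bracket in a condensed journal article is most simply a typesetting slip. The full protocol and the calculator are not shown, and every kcal figure above requires that the slip was also coded. This stands: the consequences are conditional, and a reader who inferred that CR participants are being under-restricted would go beyond the document, which does not say which form the app or the dietitians use.

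A second reply is that the cited source is not at hand, so the intended sign is inferred. This stands in part. That the printed form adds 161 is certain, while the view that it should subtract rests on the layout and the printed minus sign. Further support might be sought in the age range, "Women aged between 20 and 35 years": the printed bracket is negative below 161 / 4.92 = 32.7 years, so a term written as a subtraction raises BMR at most eligible ages. That is not independent evidence. A positive constant inside a subtracted bracket can produce this pattern, and BMR still falls with age in the printed form. It restates the layout and should carry no weight.

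Third, the ranges for TEE and target use PAL values given only as examples, and the rule linking BMI to the deficit is not stated. This also stands: those ranges are illustrative rather than bounds. Only the 322 is exact for everyone.

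The reply does not remove the point. The article chose to print the dosing formula, and a reader or site applying it literally would compute wrong targets.

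**Conclusion.** The point holds in conditional form. Equation 2 as printed adds 161, and the bracket very probably should close after the age term, subject to reference 50. If the printed form were used, BMR would be 322 kcal/day too high for every participant, TEE about 451–580 and the target about 225–406 kcal/day too high. For the assumed woman, a nominal 30% restriction would be about 14%, less than half the stated minimum.

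The conclusion rests on the layout of the equation, the example PAL values and the assumed body measurements. If the right formula is already coded, only the printed equation needs correcting.

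A reader might infer that the trial's main result is compromised, but the document does not support that. The sample size calculation and the primary intention-to-treat comparison do not use Equation 2. What could be affected is the dose delivered in the CR arm and the meaning of CR-target adherence.

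**What to change.** 1. After checking reference 50, print BMR = [9.99 × Weight] + [6.25 × Height] − [4.92 × Age] − 161.
2. Check the formula coded in the app or dietitian calculator and record the result.
3. Only if the printed form was used: correct it for participants who have not yet started, and report the restriction actually prescribed. Changing targets during a participant's intervention is a separate and debatable decision for the trial team, and this correction does not require it.
4. Keep CR-target adherence scored against the target actually prescribed, as the article defines it.

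Steps 1 and 2 cost one corrected equation and one documented check, with no new data. Step 3, if needed, would leave two prescribed dose levels within the CR arm, which the trial report would have to describe.
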